**Re-incarceration Plan:**

Correctional facility rosters will be reviewed to track re-incarceration throughout the study period, allowing the study team to locate participants who are re-incarcerated as well as determine time individual participants spend incarcerated during the follow-up period.  Should a participant be re-incarcerated or put under supervision within a correctional facility at the time a 12 or 24 week assessment visit (Study Visits 2 or 3) is due, the assessment visit will be conducted within the correctional facility if possible.  The following exceptions will be made to the standard follow-up assessment visits for those conducted within the correctional setting:

1) Blood will not be drawn for plasma vial load assessment.  Instead, the correctional facility medical record will be reviewed for a HIV PVL result within two weeks of the assessment visit.

2) No incentive or transportation vouchers will be provided for completing assessment visits while incarcerated.  The participant will have the option of picking up the $50 incentive (in the form of an American Express Gift Cheque) at the GWU study office if released prior to the completion of the funding period.

**Data Transfer and Confidentiality**

***Participant Identification***

To identify potential participants, DC DOC medical staff, discharge planners and case managers will refer HIV positive inmates to meet with GWU staff. Staff members from CBOs will also refer HIV positive ex-inmates to meet with GWU staff. Potential participants will be assigned a pre-screening ID. We will also contact interested individuals registered in the GWU Potential Participant Cohort (IRB #031140) for screening for this study. An electronic spreadsheet linking participant names and pre-screening IDs will be saved on an encrypted jump drive specifically designated to house this file and will be physically secured at the GWU Department of Epidemiology and Biostatistics offices for the duration of data collection period.

Once inmates/ex-inmates, provide consent for being screened for eligibility, are screened for eligibility, and provide consent to participate in the study, GWU research staff will enroll them in the study and assign them a unique study ID number. Study IDs will be created using alphanumeric characters and will not contain any identifying information. With the exception of locator forms and informed consent forms, these study IDs will be used to uniquely identify all study documents pertaining to a particular participant. An electronic spreadsheet linking participant names and study IDs will be saved on an encrypted jump drive specifically designated to house this file and will be physically secured at the GWU Department of Epidemiology and Biostatistics offices for the duration of data collection period. The jump drive will be stored in a locked cabinet or drawer separate from the participant files (ID numbers) and consent/locator forms (named files). Only investigators directly involved in the study at GWU will have access to the identifying information. The link file will be destroyed post-study.

***Data Collection within DC DOC Facilities and GWU research clinic space***

Participant recruitment, screening, consent, and baseline CAPI administration will be performed by trained study staff within correctional facilities or a designated, private space (e.g., at local CBOs or GW research clinic space). Given the sensitive and personal nature of the information being requested, these activities will occur in a private space or other areas in the correctional facilities and GWU research clinic space that will optimize participant confidentiality. Data collection instruments, including the study laptop computer, password-protected tablet computer, and all paper documents, will be maintained and secured by the research staff while within the facilities/ GWU research clinic space. At the end of each data collection period, all study materials will be removed from the correctional facilities or GWU research clinic space by the research staff and secured in locked file cabinets at the GWU Department of Epidemiology and Biostatistics offices.

***Post-Release Data Collection***

The initial post-release visit and follow-up Visits 2 and 3 at weeks 12 and 24 will be conducted in other private designated space (e.g., within a local CBO, such as VSC or FMCS, or in GWU research clinic space). GWU research clinic space at VSC and FMCS offices are kept locked and code-entry is required to access the research space. All data collection activities in the community, including CAPIs, locator form updating, and the collection of laboratory specimens, will occur in private rooms within the VSC/FMCS clinic spaces to ensure participant confidentiality. Data collection instruments, including the study laptop computer, the password-protected tablet computer, and all paper documents, will be secured by the research staff while on site at GWU research clinic spaces and will be secured at the GWU Department of Epidemiology and Biostatistics offices when not in use.

Information gathered during monthly check-in contact will initially be recorded on paper documents secured by the research staff. These documents will be kept in locked file cabinets at the GWU Department of Epidemiology and Biostatistics offices when not in use.

***Data Management***

GWU will maintain a secure server network drive to which only designated GWU investigators will have access. The following electronic databases will be secured on the network drive:

1. QDS^TM^ warehouse for CAPI surveys
2. Test results from testing of biological specimens
3. Monthly check-in call database
4. Clinic appointment adherence assessment database
5. Merged database (with data from #1-4)
6. Medical chart review data

*Computer-assisted Personal Interview (CAPI):*

To ensure consistency throughout the study period, GWU will develop a QDS^TM^ (Questionnaire Development System) control file with specifications for the CAPI data. QDS^TM^ is software used to program survey development, collect data, and manage data collection. At the end of each day, CAPI interview files will be uploaded into the QDS warehouse via an encrypted jump drive and subsequently deleted from both the laptop computers and jump drive. Interview files and the data warehouse are password-protected.

*Data Entry:*

With the exception of locator forms and informed consent forms, data that is initially recorded onto paper documents will be directly entered into the appropriate database on a weekly basis at the GWU Department of Epidemiology and Biostatistics offices.

*Merged Database:*

At the end of each week, the data manager will combine the above-mentioned databases into a single database. Study IDs will be used to merge the databases.

***Data Progress Reports***

The data manager will produce regular reports that contain de-identified information and summarize study activity progress. Regular data reports will be presented to GWU research staff involved in data collection activities and to Principal Investigators at GWU, Miriam Hospital, Brown University, and NYU as needed.

***Monthly Data Transfer to RI CFAR***

Data De-Identification:

Identifying information that enables the investigators to readily ascertain the identity of a study participant will be replaced with a study ID. The study ID will be a combination of numbers and letters, which will have no specific meaning pertaining to participant’s private information. The participant’s private information and the key that enables linkage of the study ID to private information will be maintained separately at the GWU study office in a locked file cabinet, which (a) will have restricted access only to the investigators at GWU under the GWU IRB policies and (b) will not be released under any circumstances to [name] and study staff at Brown University Center for Statistical Sciences.

Data Transfer:

De-identified data will be transferred directly from GWU to [name] at the Brown University Center for Statistical Sciences via a SecureTransport shared folder, to which only [name] and GWU study staff directly involved in the data transfer will be assigned password-protected user accounts. SecureTransport is a product used by the George Washington University for secure file transfer. It uses Hypertext Transfer Protocol Secure (HTTPS) and user authentication for secure communication across the internet. It has been certified Federal Information Protection Standard (FIPS) 140-2 Level 1 by the US National Institute of Standards and Technology (NIST). The secure folder will not be used for permanent data storage. De-identified data will be uploaded by GWU study staff and will remain in the folder for a maximum of 72 hours, during which time [name] will download the files before deleting them from the folder. The downloaded data will be stored on secure servers at the Brown CSS, and access will be restricted to study staff.

***Data Analysis & Presentation of Results***

Participants will be identified by their designated study IDs during all data analyses. Individual results will not be shared, and only aggregate results will be disclosed at study completion. Summary statistical data stratified by age, race or other categories may be released. An asterisk (*) will represent all cells with 3 or fewer observations. However, if the total information will allow identification of the exact person(s) represented by the asterisk, the information will not be released.

***Subject Confidentiality***

All research staff will sign confidentiality agreements prior to interacting with any study participants. All study procedures will be conducted in private, and every effort will be made to protect confidentiality and participants’ privacy to the extent possible. Also, study staff, correctional facility and CBO representatives will be encouraged to identify potential confidentiality issues and strategies to address them.

All study-related information will be stored securely at the GWU study office. All participant information will be stored in locked file cabinets and/or in lockable areas with access limited to GWU research staff. All laboratory specimens; reports; and data collection, process, and administrative forms will be identified only by a coded number to maintain participant confidentiality. All records that contain names or other personal identifiers, such as locator forms and informed consent forms, will be stored separately from study records identified by code number. All local databases will be secured with password-protected access systems. Forms, lists, logbooks, appointment books, and any other listings that link participant ID numbers to other identifying information will be stored in a separate, locked file in an area with limited access. Some members of the GWU research staff will work with participants outside of the DC DOC, the CBOs, or VSC/FMCS offices, but will follow strict procedures to limit the confidential information taken into the field and to safeguard any information collected outside of the site.

*Certificate of Confidentiality*

A Certificate of Confidentiality from the US Department of Health and Human Services will be obtained for the study. This Certificate protects study staff from being compelled to disclose study-related information by any US Federal, State or local civil, criminal, administrative, legislative, or other body.

All protected health information (PHI) will be protected according to the provisions of the HIPAA and will only be used or disclosed as allowed by the privacy rule pursuant to relevant waivers or authorizations, or as required by federal law.

***Withdrawal from the Study***

A subject may withdraw from this study at any time without prejudice. However, information collected prior to withdrawal may still be used after withdrawal.

***Study Files and Record Retention***

Link files and locator forms will be destroyed immediately post-study. Investigators will retain all additional study records at least three years, after which they will be destroyed.

**Analysis Plan**

*Summary analysis:*

Demographic characteristics (including age, gender, ethnicity, etc.) and history of prior incarceration, sexual behaviors, drug and alcohol use, and medical history (including HIV testing history, HIV/HCV status) will be summarized using means/standard deviations, medians/ranges or counts/frequencies with corresponding 95% confidence intervals (CIs) as appropriate. The summaries will be stratified by arm. An intent-to-treat analysis will be used. Baseline characteristics will be compared between control arm and corresponding comparison arm using Pearson’s Χ^2^ test for categorical variables, student’s t-test for normally distributed or Wilcoxon’s test for non-normally distributed continuous variables to assess the success of the randomization procedure. Imbalances between the study arms will be documented and investigated. Imbalanced covariates will be adjusted for subsequently through regression analysis or weighted analyses. Lost-to-follow-up (LTF) and incomplete response will also be summarized by contingency tables for each arm stratified by gender and study site, and will be compared using Pearson’s Χ^2^ test to examine whether selection bias is induced by LTF. A diagram of LTF status will be created to summarize the disposition of participants at each study visit.

*Analysis of primary and secondary outcomes:*

The longitudinal nature of the study (containing a baseline assessment before intervention and two follow-up visits after jail release) will result in repeated assessments of primary outcomes (plasma viral load suppression at Visits 2 and 3) and secondary outcomes (e.g., proportion linking to community HIV care at 30 days, 60 days, 90 days, etc.). These outcomes will be analyzed in the unified framework of generalized linear models (GLMs) with appropriate link functions (logit for dichotomized outcomes, e.g. linkage to care, detectable PVL; identify link for continuous outcomes, e.g. log-transformed PVL; or log link for count outcomes, e.g. # of non-main sexual partners). The setup of GLMs involves relating the expected outcome to a linear function of explanatory covariates, where the explanatory covariates will include a dummy variable encoding the treatment (=1) versus control (=0), dummies for study site and gender, relevant demographic covariates, and their interactions. Depending on the analysis objectives, three GLM model structures will potentially be used: 1) *Marginal models* will be used to analyze population-level intervention effect. Within-individual correlation of repeated measures will be accounted for using Generalized Estimating Equations (GEE),^6,7^ which yields consistent parameter estimates and robust standard error estimates. 2) *Random-effect generalized linear models* will be used to estimate the intervention effect at the individual-level.^8^ For those outcomes with only one follow-up visit, the model will be estimated using conditional logistic regression for binary outcomes or difference-on-difference regression for continuous outcomes for better estimation efficiencies. 3) *Markov transition models* will be used to investigate the intervention effect on the individual behavior change as previously conducted by this group,^9^ and includes the prior history of the outcomes as regression covariates; therefore, the transition model emphasizes more the effect of the intervention on outcome changes given the prior value of the outcome. Using these model setups, we will examine the different aspects of intervention for SA2 and SA3. These models will also allow us to quantify the differences between the two study sites and differences between male and female by testing the interaction between study arm and site, and potentially the interaction between study arm and gender.

*Strategy of handling missing data:* Differential LTF between arms could eliminate the randomization effect. The first round of analyses will make the “missing at random” (MAR) assumption, which states that after conditional on baseline covariates, there is no systematic difference between those LTF and those retained in the study. With the MAR assumption, we will construct logistic regression models that express “missingness” as a function of covariates, and use the logistic model to calculate the propensity score for “missingness” for each individual. We will use the propensity score in terms of inverse probability weighting to adjust for the selection bias due to missing data in our regression analysis.^10^ Afterwards, we will relax the MAR assumption by conducting a sensitivity analysis through considering a family of plausible “not missing at random” models using the techniques outlined by Diggle and Kenward^11^ and Daniels et al.^12^

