**Enrollment goal:**

We plan to enroll, over a 2-year study period, up to 150 HIV-infected detainees and recently-released ex-detainees within the DC Department of Corrections facilities and in the community. Participants will be enrolled inside the DC Department of Corrections (DOC) facilities and or in other private designated space (e.g., within a local CBO or in GWU research clinic space) in the community within 6 months of release from a correctional facility.

Detainees will be recruited from the Central Detention Facility (CDF) or from the Correctional Treatment Facility (CTF), both under the jurisdiction of the DC DOC. These facilities together will be referred to from here on as “DOC”. Correctional facilities refer to jail, prison, halfway houses and other restricted settings. Recently-released ex-detainees will be recruited from local community-based organizations (CBOs) that work closely with returning citizens and venues that cater to this population (see below) (see attached letter of support from the Visitors’ Services Center: Appendix O).

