***Baseline visit 2:***

Within 1 week of baseline visit 1, participants will complete baseline visit 2, which includes random assignment to the study arm, updates to the study locator information, and medical chart review. Depending on the operational time constraints in the facility and in the community GWU research space (some of which is rented from local CBOs), baseline visit 2 may occur immediately after the screening, consenting, and enrollment process, as determined by the facility or depending on time constraints at the GWU research clinic space.

For participants recruited in the community, a blood draw will be conducted to provide a baseline measurement of plasma viral load and CD4 cell count (baseline only) (see 12-week/24-week study visit section for description about blood draw). Study participants will be randomized at this point to either the 1) intervention arm or 2) the control arm. A 1:1 block randomization scheme will be created using a SAS program to select random assignments. Blocks of 4 will be used to ensure equal population of each group during the course of the study. The study coordinator will manage the randomization list. Prior to the visit, the RA will consult with the study coordinator for the randomized assignments. At the beginning of this visit with the participant, the RA will administer either the intervention (CARE+ Corrections tool) or the control condition to the participant based on their assignment.

- Intervention Arm:

Participants will complete the CARE+ Corrections counseling session, which will last less than 30 minutes. The CARE+ Corrections session will consist of the following:

- The CARE+ Corrections tool is a computerized, one-session motivational interview (for an outline of the CARE+ Corrections tool, see Appendix F: CARE+ Corrections Flow Chart and Excel Spreadsheet).

- The CARE+ Corrections session will be conducted using a laptop computer or tablet with a touch screen and consists of an audio-assisted session in which participants provide responses to questions about demographic characteristics, sexual risk behaviors and attitudes, substance use, mental health, and HIV treatment and adherence.
- After the computerized assessment is completed, the CARE+ Corrections tool will provide tailored feedback based on their responses to the above questions.

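### Adjustment covariates are chosen from baseline tests between randomised arms, and the listed outcome-model terms omit baseline viral suppression and, read plainly, include arm interactions

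*Protocol*

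**What the plan says.** Under *Summary analysis* in the protocol's Analysis Plan, baseline characteristics are compared between arms by chi-square, t or Wilcoxon tests "to assess the success of the randomization procedure". Imbalances are documented and investigated, and then: "Imbalanced covariates will be adjusted for subsequently through regression analysis or weighted analyses". There is no list of covariates and no threshold. The tests are the only criterion of imbalance given.

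Under *Analysis of primary and secondary outcomes*, the outcome is "primary outcomes (plasma viral load suppression at Visits 2 and 3", that is, at 12 and 24 weeks. For the outcome models, "the explanatory covariates will include a dummy variable encoding the treatment (=1) versus control (=0", followed by "dummies for study site and gender, relevant demographic covariates, and their interactions". Baseline viral load is not named. On model choice, "three GLM model structures will potentially be used": a marginal GEE model for the population-level effect, a random-effects model, and a Markov transition model that takes earlier outcomes as covariates. None is called primary. The section ends by saying that arm-by-site, and potentially arm-by-gender, interactions will be tested.

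Baseline viral load is measured. Community recruits have it drawn at the randomisation visit (*Baseline visit 2*). Jail (DOC) recruits have it drawn at the *Post-release visit*, after randomisation and after the tablet or video session.

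**The concern.** Three features of the stated plan weaken the main estimate.

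- **Selection by test.** Between properly randomised arms, a significant baseline difference is a chance finding. A p-value for imbalance does not show whether the covariate predicts outcome, so the rule can add irrelevant variables and leave out useful ones. Whether to regress or to weight is also left until after the comparison.
- **Baseline suppression not named.** Suppression before the intervention is an obvious candidate predictor of suppression after it. The list shared by all the models omits it. Only the transition model explicitly conditions on the prior outcome, and at 24 weeks its natural prior value is the 12-week result, which treatment may already have changed. It therefore does not replace baseline adjustment of the overall effect.
- **Arm interactions.** The treatment dummy stands in the same list as site, gender and demographics, so *their interactions* naturally covers arm-by-site and arm-by-gender. With 0/1 dummies the arm coefficient is then the effect for one gender at one site, not the population-level effect that the GEE model is meant to give.

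At stake are power in a trial of at most 150 people and an estimate that is not fixed before the data are seen.

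**Working it through.** The protocol gives no alpha, power, effect size or suppression rate, so there is no figure of its own to reproduce. The size has to be shown under assumptions.

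**Inputs from the protocol.** Sample size: "up to 150 HIV-infected detainees and recently-released ex-detainees" (*Enrollment goal*). Allocation: "A 1:1 block randomization scheme will be created using a SAS program to select random assignments", in blocks of 4 with no stratification factor stated (*Baseline visit 2*). The outcome is binary suppression.

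**1. Chance flags.** With k independent tests at an assumed 5% level, P(at least one flag) = 1 − 0.95^k.

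| k | P(at least one) |
|---|---|
| 5 | 0.226 |
| 10 | 0.401 |
| 20 | 0.642 |

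The number of variables to be tested is not stated, so k is illustrative.

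**2. Adjustment for baseline suppression.** Simulated logistic regression: one visit, 1,000 runs, two-sided 5%, 50% suppressed at baseline, arm odds ratio 2.5 conditional on baseline, and baseline-outcome odds ratio (OR) 2, 5 or 10. The test-driven rule adjusts only if the baseline difference has |z| > 1.96. Power of the arm test:

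| N | Baseline OR | Never adjusted | Adjusted if test significant | Pre-specified | Gain, pre-specified minus never (points) |
|---|---|---|---|---|---|
| 150 | 2 | 73.0% | 72.8% | 72.2% | −0.8 |
| 150 | 5 | 67.5% | 67.7% | 73.8% | 6.3 |
| 150 | 10 | 54.6% | 54.9% | 63.2% | 8.6 |
| 110 | 2 | 62.9% | 63.0% | 64.5% | 1.6 |
| 110 | 5 | 51.2% | 52.0% | 58.1% | 6.9 |
| 110 | 10 | 40.6% | 40.5% | 50.4% | 9.8 |

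The Monte Carlo standard error of a power near 70% is √(0.7 × 0.3 / 1000) = 1.4 points, so the OR 2 rows show no real difference. Test-driven adjustment performs like no adjustment.

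**3. Type I error.** With no arm effect, the test-driven rule rejected in 4.9%, 3.6% and 3.6% of runs at N=150 and in 5.9%, 4.4% and 3.7% at N=110. There is no inflation.

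**4. Arm interactions.** If a fraction ps of participants is outside the reference site and pg outside the reference gender, the variance of the arm coefficient relative to a main-effects model is approximately 1 + ps/(1 − ps) + pg/(1 − pg). With ps = 0.5 and pg = 0.4 (assumed), this is 1 + 1 + 0.667 = 2.667, so the standard error is multiplied by √2.667 = 1.63. The simulation agrees. At N=150 with no true interactions, the median standard error rises from 0.349 to 0.577 (OR 2), 0.346 to 0.572 (OR 5) and 0.343 to 0.568 (OR 10), a factor of about 1.65. Power of the arm coefficient falls from 72.5% to 35.5%, 67.6% to 30.8% and 53.5% to 23.6%.

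**The case against.** The strongest case against is that the detailed covariate list normally belongs in the SAP, which is not shown. The list opens with *will include* and need not be complete, no model is designated primary, and *their interactions* may mean covariate-by-covariate terms, since the arm interactions get their own sentence later. Much of this stands, and it rules out several stronger readings.

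- A reader might infer that the primary model omits baseline suppression. The protocol names no primary model. It can only be said that the common list, and hence the GEE model as described, does not name it.
- A reader might infer that arm interactions are definitely in the main model. That is the plain reading but not a certain one. The loss in step 4 also requires someone to report the reference-cell coefficient as the trial result, which the protocol does not say.
- A reader might infer that test-driven selection inflates false positives. Step 3 gives no support for that.
- A reader might apply the linear-model factor 1 − r² and claim a large cut in variance. On the logit scale the arm term's standard error rises on adjustment (0.341 to 0.375 at OR 5, N=150). Power rises because the conditional log-odds ratio is larger. Nor does the protocol say that baseline suppression is the strongest predictor.
- A reader might take the two study sites to be jail and community recruitment. That is an inference: the protocol also has two DOC facilities and two named community spaces.

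The random-effects option does mention conditional logistic and difference regressions, which would use baseline values, but only for outcomes with a single follow-up visit. Suppression has two.

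The objection does not reach the adjust-if-imbalanced rule. The protocol states that rule outright, so it is not a detail awaiting the SAP.

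**Conclusion.** The point holds in a limited form and should be corrected. The test-driven adjustment rule is stated and has no advantage: in the simulations it performed like never adjusting, and it leaves both the covariates and the method of adjustment open. Leaving baseline suppression out of the common list costs between nothing and about 9 power points at N=150 for assumed baseline odds ratios of 2 to 10. If arm interactions are meant, and the arm coefficient is then read as the overall effect, its standard error is about 1.65 times as large and it answers a different question.

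These sizes rest on an assumed arm odds ratio of 2.5, 50% baseline suppression, site split 50/50, gender split 60/40, no true interactions, one visit and a baseline value available for everyone. The last assumption is optimistic for jail recruits. The damage is to power and to a fixed estimate. The documents and the calculations do not support a claim of raised type I error.

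**What to change.** 1. Describe baseline balance by arm and do not use tests to choose covariates. Delete the adjust-if-imbalanced sentence.
2. Name one main model for viral suppression: GEE logistic with arm, visit, arm-by-visit, gender, recruitment setting (DOC or community) and baseline suppression. Because arm-by-visit is in the model, state which contrast is the main result (12 weeks, 24 weeks or their average), so that the reference-category problem does not return through visit.
3. Put arm-by-site and arm-by-gender terms only in separate secondary models.
4. Define baseline suppression by recruitment route. For community recruits, use the baseline draw and specify that it precedes the assigned session, since *Baseline visit 2* does not settle the order clearly. For DOC recruits, use the last viral load before randomisation from the chart review of the 12 months before enrolment, where available, with a missing category otherwise. Do not use the post-release draw as a pre-randomisation covariate: it follows randomisation and the session, and is missing for those who do not attend.
5. Define *study site*, or replace it with recruitment setting.

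The cost is mainly wording in the protocol or SAP, plus a check that the chart abstraction form captures dated viral loads. The downside is that chart values for DOC recruits may be older or missing, which would reduce the gain.

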**Study Timeline:**

Up to 150 participants will be enrolled in the study. Recruitment will begin in August 2013 for 18-24 months, and follow-up visits will conclude in August 2015. Data analysis and dissemination will commence soon after the first follow-up visit and will continue through to the end of the study (June 2015).

| **Activity** | **Time frame** |
| --- | --- |
| IRB submission | June 2012 |
| IRB approval | September 2012 |
| Recruitment | August 2013 – February 2015 |
| Follow-up visits (12 and 24 weeks) | November 2013 – August 2015 |
| Data analysis and dissemination | August 2013 – June 2016 (with no cost-extension) |

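### For outcomes with one follow-up visit, conditional logistic and difference-on-difference regression are chosen for efficiency, but both are less efficient than adjusting for baseline

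*Protocol*

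**What the plan says.** The Analysis Plan describes the design as "containing a baseline assessment before intervention and two follow-up visits after jail release". It states that "three GLM model structures will potentially be used": marginal models fitted by GEE, random-effect models, and Markov transition models.

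The rule at issue belongs to the second structure. It opens with "For those outcomes with only one follow-up visit" and prescribes "conditional logistic regression for binary outcomes or difference-on-difference regression for continuous outcomes for better estimation efficiencies". It does not say which alternative these methods are more efficient than.

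Two neighbouring statements limit its reach. The primary outcome is planned as "repeated assessments of primary outcomes (plasma viral load suppression at Visits 2 and 3"), so it has two follow-ups. The third structure, the transition model, "includes the prior history of the outcomes as regression covariates", which with one follow-up is already a baseline-adjusted regression.

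**The concern.** With one baseline and one follow-up value per person, both prescribed methods remove stable differences between people by working within the person. That is useful when the arms may differ systematically at baseline. Here arm is randomised, so there is no such confounding to remove, and what matters is precision.

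On precision the stated reason points the wrong way. Differencing subtracts the whole baseline value, although only a fraction of it (the regression slope) predicts follow-up. Conditional logistic regression sets aside everyone whose status is the same at both times. At stake is the precision of any secondary outcome analysed under this rule, in a trial where "Up to 150 participants will be enrolled in the study".

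**Working it through.** **Inputs from the protocol.** At most 150 participants (Study Timeline), allocated 1:1 (Baseline visit 2), so 75 per arm at full enrolment. The protocol gives no efficiency or power figure to reproduce. It also gives no pre/post correlation, event rates or effect size.

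**Assumed.** Two-sided 5% level, no dropout, an effect of 0.4 SD for continuous outcomes, and the rates and correlations shown below.

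**Continuous outcomes.** Let sB and sF be the baseline and follow-up SDs and rho their correlation.

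- Variance of the change: sF² + sB² − 2·rho·sB·sF.
- Residual variance after baseline adjustment: sF²(1 − rho²).
- Difference between the two: (sB − rho·sF)², which is never negative. Differencing can at best tie, when sB = rho·sF.
- With sB = sF the ratio is 2(1 − rho)/(1 − rho²) = 2/(1 + rho).
- Against ignoring baseline altogether the ratio is 2(1 − rho), which exceeds 1 when rho is below 0.5.

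Power is Φ(0.4/(SD·√(2/75)) − 1.96). At rho 0.3 the SD of the change is √1.4 = 1.183, giving Φ(2.07 − 1.96) = 54%. The adjusted SD is √0.91 = 0.954, giving Φ(2.57 − 1.96) = 73%.

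| rho | Variance ratio | Power, difference | Power, baseline-adjusted | Power, follow-up only |
|---|---|---|---|---|
| 0.3 | 1.54 | 54% | 73% | 69% |
| 0.5 | 1.33 | 69% | 81% | 69% |
| 0.7 | 1.18 | 89% | 93% | 69% |

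Put as sample size, a difference analysis of 150 people carries the information of about 98 (150/1.54) at rho 0.3, or 113 (150/1.33) at rho 0.5, analysed with baseline adjustment.

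**Binary outcomes.** With one pre/post pair, the conditional likelihood reduces to the direction of change compared between arms, among people who changed. Their share is p0 + p1 − 2·p11, where p11 = p0·p1 + phi·√(p0(1−p0)p1(1−p1)), capped at the smaller of p0 and p1. For baseline rates of 0.3 to 0.6, follow-up rates of 0.4 to 0.7 and phi of 0 to 0.6, the share runs from 19% to 58%.

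Power was simulated with 150 people, 3,000 trials per scenario, a random-intercept logistic model, a baseline rate of 50% and a time effect of 0.3 on the log-odds scale. The first figure in each power cell is from a Wald test. For conditional logistic regression that test counted trials with an empty cell as non-significant, which was 18% of trials in the last row. I therefore re-simulated the same scenarios with likelihood-ratio tests; this is the second figure.

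| Intercept SD, log-odds effect | Share changing | Conditional logistic | Baseline-adjusted logistic | Follow-up only |
|---|---|---|---|---|
| 0.5, 1.0 | 48% | 47% / 49% | 76% / 77% | 76% / 77% |
| 1, 1.0 | 42% | 42% / 44% | 69% / 68% | 68% / 67% |
| 2, 1.5 | 33% | 55% / 63% | 82% / 83% | 76% / 77% |
| 3, 1.5 | 25% | 41% / 53% | 66% / 68% | 56% / 55% |
| 4, 2.0 | 22% | 39% / 62% | 77% / 79% | 61% / 60% |

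With no effect (intercept SD 1, 2 and 3), the Wald tests rejected in 4.3% to 5.0% of trials for conditional logistic and 4.7% to 5.5% for baseline-adjusted regression. The gain is therefore not bought with false positives.

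A separate simulation without a random intercept (baseline 50%, follow-up 50% against 70%, phi 0.3 to 0.5) gave the same order: 26% to 36% of people informative, with power of 55% to 61% for conditional logistic and 75% to 81% for baseline-adjusted regression.

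**The case against.** **The rule may cover nothing important.** It sits in one of three structures that are only potentially used, and it is limited to one-follow-up outcomes. Viral load and the follow-up interview are both scheduled at 12 and 24 weeks, and the protocol names no outcome with a baseline and exactly one follow-up. This stands as a limit on scope. It does not make the rule right, because the protocol provides for such outcomes and fixes their analysis.

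**No comparator is named, so the text never claims to beat baseline adjustment.** That is true of the wording. But differencing beats only an analysis that ignores baseline, and at equal variances only when rho exceeds 0.5. Conditional logistic regression has a real merit, in that it needs no assumption about how the person effects are distributed, but that is robustness and not efficiency.

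**The two binary models estimate different things.** Conditional logistic regression gives a within-person odds ratio, the other an odds ratio conditional on baseline. This stands, and is why they are compared on power and not on the variance of a coefficient. It supports keeping conditional logistic regression for that purpose, without the efficiency claim.

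**Stronger readings a reader might draw.** The documents do not support these:

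- That both methods discard most participants. Difference-on-difference drops nobody who has both values. For conditional logistic regression a majority is likely under positive correlation, but the share rests on rates the protocol does not give.
- That conditional logistic regression always does worse than ignoring baseline. With likelihood-ratio tests the last scenario gives 62% against 60%.
- That linkage to care would be analysed this way. The protocol does not say so.

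**Conclusion.** The efficiency rationale is wrong and should not decide the method. For continuous outcomes the direction is algebraic: differencing is never more precise than baseline adjustment. Its size, a variance 33% to 54% larger at correlations of 0.5 to 0.3, assumes equal variances before and after. For binary outcomes the finding rests on simulation under assumed rates. Conditional logistic power was below baseline-adjusted power in every scenario, by roughly 15 to 28 percentage points with likelihood-ratio tests.

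These figures illustrate the methods and do not measure this trial's loss. A reader might infer that power for viral suppression is affected. It is not, because that outcome has two follow-up visits and falls outside the rule. Nor does this point decide which of the three structures should be primary. It warrants correcting one rule for secondary analyses.

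**What to change.** Replace the sentence with a rule of this kind: for outcomes with one follow-up visit, fit logistic (binary) or linear (continuous) regression of the follow-up value on arm and the pre-randomisation value of the outcome, with the site and gender terms already planned. Delete the efficiency rationale.

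Omit the baseline term for outcomes with no pre-randomisation value. This matters for people recruited in jail: under Baseline visit 1, Baseline visit 2 and Post-release visit, their study blood draw and Community Baseline interview come after the intervention session. Those values may already carry some of the effect and should not be used for adjustment.

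The cost is one sentence in the protocol or SAP and no new data. The drawback is that the binary estimate becomes an odds ratio conditional on baseline, not a within-person one. If the within-person estimate is wanted, keep conditional logistic regression as a supportive analysis and say that this is its purpose.
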